## Materials and methods

### Sample and sampling procedure

Participants for the current study will be selected from a community sample of participants from Berlin, Germany that were recruited for the first phase of the CovSocial project (Details of the study site can be obtained from the ClinicalTrials.gov by accessing the study record at https://clinicaltrials.gov/ct2/show/NCT04889508). Participants for the first phase of the project were recruited from the population of the city of Berlin, Germany. The main inclusion criteria involved being between 18 and 65 years of age, being able to understand the German language, and to be registered as a resident of the city of Berlin at the time of the assessment. We used a variety of methods for recruitment including sampling 56,000 individuals from the Berlin registration office, flyers and posters, and advertising on social media, in addition to the chain-referral method. The recruitment led to the registration of 7214 individuals to take part in the study. Out of this, only 5877 started the questionnaires, and at every block of questionnaires we saw further dropout in sample. A total of 3681 individuals completed the questionnaires for the first three timepoints of the first phase of the study. Lastly, participants were excluded for not meeting the inclusion criteria and for data quality reasons, leading to a final sample of 3522 individuals for the first three timepoints of the first phase of the project. Please see S1 Appendix for the number of participants at each further timepoint T4-T7, and all participants who also completed the genome-wide marker assessment.

Participants for the second phase will now be recruited from this initial sample, and assigned to one of the three groups, socio-emotional intervention group, mindfulness-based intervention group, and retest control group (waitlist control), in the following sequential steps (please see Fig 4).

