
An estimated 300 individuals, 100 per intervention group, will be recruited. A priori effect size and power calculations have been performed based on the results from the previous mental training study, the ReSource project [67], which developed and validated the interventions being applied in the current study. Power analyses were conducted using G*Power [194] for analysis of variance with repeated measurements and interactions between group and intra-group variables. The analyses elements were as follows: an alpha level of .05, with a power (1-ß) of .80, 3 groups and 2 measurement occasions, a correlation of variables with repeated measurements of .39 which is the lower limit of retest reliability for the Cortisol Awakening Response (CAR; [195]), and an assumed small effect size of *f* = .10. This results in a total sample size of *n* = 297. For the additional third measurement time (post-test 2 following socio-emotional intervention given to waitlist control group) power analysis was conducted in a similar manner as above.

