#### Effects of mental training interventions on pre-post changes in variables of interest

In order to evaluate intervention-related effects on variables of interest, a mixed-effects modeling approach will be applied. Effects of time of assessment (pre-test/post-test for primary outcome variables and pre-training session/post-training session for secondary outcome variables respectively) and intervention group (socio-emotional mental training/mindfulness-based mental training/waitlist control group), as well as the interaction between time and group will be defined as fixed effects. Dummy coding with the waitlist control group as reference will be used for the intervention group variable. Additionally, we will control for participant-related random effects.

In addition, latent change scores for each primary outcome variable respectively will be computed with two timepoints (pre-test/post-test). The change in outcomes will be modeled as a latent variable and this latent change will be predicted by the treatment condition (path c in Fig 6). A correlation between the latent change score and initial levels on the primary outcome variable of interest is evaluated.

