#### Background, context and socio-demographic variables

Where necessary, we will account for socio-demographic variables (such as age, gender, marital status, number of children, education in years, and household income) and other context variables including COVID-19 related questions (e.g., access to green spaces, job status, covid-related health status, living situation, financial and job risk factors etc.) assessed in the context of the extensive assessment in phase 1. Predictive value of relevant context- and demographic variables on differences in variables of interest at pretest and their training-related change will be explored similarly to the prediction by latent trait factors assessed in phase 1. Besides, initial levels on outcome variables of interest at pretest will be controlled for by including autoregressive paths in respective models.

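### The 80% power figure allows for only 1% loss after the pre-test and covers only the joint group-by-time test, and the plan does not tie its mixed model to baseline adjustment

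*Protocol article*

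**What the plan says.** **Sample size.** The power paragraph of 'Sample and sampling procedure' states: "An estimated 300 individuals, 100 per intervention group, will be recruited". The calculation is for "analysis of variance with repeated measurements and interactions between group and intra-group variables". Its settings are "an alpha level of .05, with a power (1-ß) of .80, 3 groups and 2 measurement occasions". The assumed effect is f = .10, and the stability of the outcome between occasions enters as "a correlation of variables with repeated measurements of .39 which is the lower limit of retest reliability for the Cortisol Awakening Response". The result is 297.

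**Replacement.** 'Procedure' fills gaps to 100 per group after the screening calls and says that this completes recruitment. The pre-intervention saliva and EMA period, the lab visit and the questionnaires come afterwards. No allowance is stated for loss between pre-test and post-test.

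**Analysis.** The section on effects of the interventions on pre-post changes specifies a mixed model with time, group and their interaction as fixed effects. Group is dummy-coded against the waitlist, and there are participant random effects. The section adds a latent-change model in which treatment predicts change, and says: "A correlation between the latent change score and initial levels on the primary outcome variable of interest is evaluated". Later, 'Background, context and socio-demographic variables' says that "initial levels on outcome variables of interest at pretest will be controlled for by including autoregressive paths in respective models".

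**Hypotheses.** 'Stress' and 'Loneliness and social connectedness' expect the socio-emotional training to do better than the mindfulness training on cortisol, loneliness and connectedness.

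**The concern.** Three things in the plan do not fit together.

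- The required number counts complete pairs, and recruitment exceeds it by three people. The participants then face ten weeks of practice six times a week (trained arms), a second lab visit and a second saliva period. Withdrawal is possible at any time, and adverse events lead to exclusion.
- The powered test is a joint test on 2 df. The coding yields two 1-df contrasts against waitlist, and the head-to-head hypotheses concern a third contrast. No power is given for any of them.
- The text does not settle whether the mixed model conditions on the pre-test. At a pre-post correlation of .39 this choice changes the variance by about 30%.

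A reader who relies on 80% power would misjudge what a null result means, above all for the comparison of the two trainings.

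**Working it through.** **Inputs from the protocol:** k = 3 groups, m = 2 occasions, alpha = .05, rho = .39, f = .10, N = 297 required, 300 recruited. **Assumed:** loss after the pre-test of 10, 15 or 20%; the pattern of arm means; outcome SD = 1.

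**1. The plan's figure.** For the within-between interaction, lambda = f²·N·m/(1 − rho), with df = (k − 1)(m − 1) = 2 and (N − k)(m − 1).

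At N = 297, lambda = 0.01 × 297 × 2/0.61 = 9.74 with df 2 and 294, and power is 0.8002. At 294, the next lower multiple of three, it is 0.796. The stated 297 is therefore reproduced. At 300, power is 0.804. The margin is 3/300 = 1%.

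**2. Loss of pairs, same formula.**

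| Loss from 300 | Pairs | Power, joint test |
|---|---|---|
| 10% | 270 | 0.758 |
| 15% | 255 | 0.732 |
| 20% | 240 | 0.704 |

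**3. What f = .10 means for single contrasts.** With two occasions, the root-mean-square deviation of the group changes from their mean is 2f = 0.2 SD.

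- Both trainings equally effective (d, d, 0): d = 0.2/√(2/9) = 0.424 SD.
- Evenly spaced (d, d/2, 0): d = 0.2 × √6 = 0.490 SD, so adjacent arms differ by 0.245 SD.

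The change-score variance is 2(1 − rho) = 1.22. The standard error of a pairwise contrast at 100 per arm is √(2 × 1.22/100) = 0.156. Two-sided noncentral t with pooled df gives:

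| Contrast | Difference | Power, change score | Power, baseline-adjusted |
|---|---|---|---|
| Each training vs waitlist, equal effects | 0.424 SD | 0.773 | 0.901 |
| Better training vs waitlist, evenly spaced | 0.490 SD | 0.878 | 0.963 |
| Training vs training, evenly spaced | 0.245 SD | 0.346 | 0.466 |

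**4. Baseline adjustment.** The adjusted variance is 1 − rho² = 1 − 0.1521 = 0.848. Its ratio to the change-score variance is 0.848/1.22 = (1 + rho)/2 = 0.695, and the pairwise standard error is √(2 × 0.848/100) = 0.130. Dividing lambda by 0.695 gives joint-test power of 0.928 at 300, 0.859 at 240 and 0.806 at 210.

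**5. Which planned model does what.** A time × group random-intercept model with free pre-test means was fitted to simulated data (N = 300, rho = .39). It returned the same contrasts and the same standard error (0.1585) as a regression of change scores on group; the baseline-adjusted standard error was 0.130.

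The latent-change model as described has a path from treatment to change, a change-baseline correlation, and no stated path from treatment to baseline. In a second simulated data set it gave 0.57616 and 0.36846. Covariance analysis gave the same two values, and change scores gave 0.57621 and 0.41382. As described, it is already a baseline-adjusted analysis.

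**The case against.** Much of the other side's case limits the point, and these parts stand.

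- **Complete pairs are the worst case.** If the mixed or structural model is fitted by likelihood to all available data, and data are missing at random, pre-only participants contribute. Per arm with n pairs out of 100, the variance of the estimated change is (1 − rho²)/n + (1 − rho)²/100. Joint-test power is then about 0.77, 0.75 and 0.73 at 10, 15 and 20% loss.
- **The correlation is conservative.** The protocol calls .39 a lower limit for the cortisol awakening response. With an assumed rho of .6, power at 240 pairs is 0.88. The shortfall concerns outcomes as noisy as that one.
- **The article is condensed.** Contrast-level power and exact model specification may stand in files not shown. Even so, the sample-size argument is given in full here and leaves no room for loss.

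A reader might also infer four stronger things that the protocol does not support.

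- **That the plan does not use the powered test.** The interaction is a planned fixed effect. Dummy coding fixes the parametrisation and does not exclude a joint test, which is simply not named.
- **That the plan discards baseline information.** This is true only of the mixed model with free pre-test means. It is not true of the latent-change model as described, and the later section promises control for initial levels. What is missing is any statement that this control extends to the mixed model.
- **That phase 1 predicts the loss.** "A total of 3681 individuals completed the questionnaires for the first three timepoints" out of 5877 who started, a loss of 1 − 3681/5877 = 37%. That was a mass-recruited questionnaire cohort. Phase 2 draws on its completers, screens them, obtains consent, pays for testing time and gives the trained arms weekly sessions.
- **That baseline adjustment recovers all lost power.** It does so for the joint test and the 0.424 SD contrasts, but not for training versus training.

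**Conclusion.** The point holds in a limited form. The 297 is correct for what it computes, but it is a number of completers, with a 1% margin and no replacement after the pre-test. At rho = .39 and an assumed 10 to 20% loss of pairs, joint-test power is about 0.76 to 0.70, and somewhat higher under likelihood estimation or a larger correlation.

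The 80% does not carry over to single contrasts. At 100 per arm and f = .10 they range from 0.35 to 0.88, depending on the pattern of means. The comparison between the trainings, which the hypotheses rely on, is at the low end if effects are evenly spaced.

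The mixed model as written is a change-score analysis, and the protocol's promise of control for initial levels is not tied to it. All figures assume equal arms, equal variances at the two occasions and the protocol's f and rho.

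**What to change.** 1. **Analysis.** State that the primary mixed model conditions on the pre-test, either as a covariate or by constraining pre-test means to be equal across groups. State that baseline is not freed by group in the latent-change model, and that the autoregressive control in 'Background, context and socio-demographic variables' refers to these models. Name the joint interaction test if it is intended.
2. **Power statement.** Give 80% at 297 completers for the joint test, the values under assumed loss, and the values for each training versus waitlist and for training versus training, with and without baseline adjustment. Say plainly that training versus training remains at about 0.47 for 0.245 SD even after adjustment.

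The cost is a change of wording and a restated figure; enrolment, visits and treatment stay as they are. The drawbacks are that the stated power looks less favourable, and that baseline adjustment presumes a pre-test not influenced by allocation. The second needs attention because participants know their group before the pre-test.

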### Study design and setting

We will use a multi-factorial mixed (between- and within-subjects) design. Type of intervention will serve as the between-subjects variable. Type of intervention has three levels: 1) socio-emotional mental training intervention, 2) mindfulness-based mental training intervention, and 3) retest control group (waitlist control). Within-subjects effects, from pre- to post-intervention, will be assessed on dependent variables of interest. Participants in intervention groups 1 and 2 will be assessed on dependent variables at 2 timepoints, pre and post the intervention period (pre-test & post-test). The waitlist control group will be assessed on dependent variables at 3 timepoints, i.e., as retest control group at pre and post the first intervention period (pre-test and post-test) and post a second socio-emotional intervention period, which only applies to this group (post-test 2). Participants will be randomly assigned to one of the three groups in a parallel group design using computer generated numbers in a block randomization technique with 1:1:1 allocation. No blinding will be used since both participants and staff need to be aware which condition the participant belongs to in order to be able to attain and provide the appropriate training and practice prior to starting the actual interventions. The study will be conducted at the Social Neuroscience Lab, Max Planck Society, Berlin, Germany. The study will take place online, with the exception of lab visits for administration of behavioral tasks (2 for groups 1 and 2, 3 for group 3).

#### Ethics approval and consent to participate

The study will be conducted in accordance with the Declaration of Helsinki, and all participants will provide written informed consent prior to their participation in the study. Participation in the study is fully voluntary, and withdrawal from the study is possible at any time. Participants will be reimbursed for the time spent on the testing portion of the study at the rate of 10 euro per hour. The study protocol has been approved by the ethics commission of the Charité –Universitätsmedizin Berlin (EA4/081/21). Modifications of the protocol are reported to the committee. Please see S1–S4 Files for study protocol and the amendment submitted to the ethics commission. The trial is registered at clinicaltrials.gov (NCT04889508). The study is a controlled clinical trial with a retest control condition and will follow the Standard Protocol Items: Recommendations for Interventional Trials (SPIRIT) Statement for reporting trial protocols (see S5 File).

### Measures

Please see Fig 5 for an overview of which measures will be administered when during the study protocol.

**Fig 5 pone.0256323.g005:**
[figure not shown]
An overview of which measures will be assessed when during the study. Red circles indicate the pre-intervention testing phase, wherein participants will complete the first round of pre-post questionnaires, pre-post behavioral tasks, pre-post EMA and pre-post epigenetic marker assessment. The pink circle indicates the post-intervention testing phase, wherein participants will complete the second round of these measures. The 10 yellow circles indicate the weekly assessments during the intervention. The small solid yellow circles indicate the daily assessments pre and post daily intervention exercise.

#### Pre-post questionnaires

We will assess change from baseline to 10 weeks after the intervention using the following validated questionnaires which will be administered at pre-test, post-test and post-test 2: Perceived Stress Scale-10 (PSS-10; [196]), UCLA Loneliness Scale [197]), Beck Depression Inventory-II (BDI-II; [113]), Connor-Davidson Resilience Scale (CD-RISC; [136]), State-Trait Anxiety Inventory (STAI; [114]), Cognitive Emotion Regulation Questionnaire (CERQ; [198]), Difficulties in Emotion Regulation Scale (DERS; [199]), Brief Resilience Scale (BRS; [137]), Prosocialness Scale for Adults (PSA; [200]) Multidimensional Assessment of Interoceptive Awareness (MAIA; [201]), Fear of Compassion Scale (FoC; [202]), Sussex-Oxford Compassion Scales (SOCS; [203]), State Self-Compassion Scale–Long Form (S-SCS; [204]), Interpersonal Reactivity Index (IRI; [205]) and Toronto Alexithymia Scale (TAS-20; [189]). The following COVID-19 related self-generated questions will also be assessed: belonging to COVID-19 biological risk group, belonging to COVID-19 professional risk group, positive test result for COVID-19, presence of COVID-19 symptoms, hospitalization due to COVID-19 and the duration of hospitalization, the history of or current presence of long-covid symptoms, status of COVID-19 vaccination (received none, first or both doses), perception of benefits of COVID-19 vaccination (in case of one or two doses received), willingness to receive COVID-19 vaccination (in case of no vaccine dose received), and impact of COVID-19 related restrictions and limitations. Participants will also answer questions regarding their smoking behavior, alcohol consumption behavior (using AUDIT-C; [206]), current pregnancy (if any), use of hormonal medication, presence of endocrine disorders, oral contraceptive use, and Body Mass Index (BMI). The questionnaires will be completed using a mobile and web app.

#### Pre-post behavioral tasks

The behavioral tasks will be administered in person in lab. We will assess change from baseline to 10 weeks after the intervention using the following behavioral tasks:

EmpaToM [152]: This task allows to simultaneously measure empathy, compassion and theory of mind (ToM). It consists of 48 emotionally neutral or negative short video sequences. Valence (empathy) and feelings of compassion (compassion) will be rated by participants, followed by multiple choice questions that demand a ToM-inference or factual reasoning.Zurich Prosocial Game [166]: This game serves as implicit assessment of prosocial behavior in the context of reciprocity, helping cost and distress cues. Measure of interest is the number of keys that a participant invests in removing obstacles from another player’s maze path when no reciprocity is given, independent from reciprocity (percentage of times the other player removed obstacles of the participant’s maze) and helping cost (percentage of times when helping costs keys left for one’s own maze). This altruistic prosocial behavior is assessed in two conditions, i.e., with and without distress cues.Social Value Orientation [207]: Participants are asked to allocate money between themselves and another person. Thereby, participants choose between three distribution options (prosocial = optimizing other’s gain; individualistic = optimizing one’s own gain; competitive = maximizing the difference in gains). The task will be conducted in 9 rounds. Number of prosocial choices will be the measure of interest.Social Discounting [208]: For each of 7 imagined acquaintances of different social distances to them, participants will distribute money to either themselves or another person and themselves in 9 different settings. Distribution choices can be either selfish or generous. The crossover point between last selfish and first altruistic choice represents the amount they are willing to forgo for another person. The degree of discounting (k) under the assumption of a hyperbolic function between social distance and money distributed to others will serve as variable of interest.Scrambled Sentences Task (SST; [135]): Scrambled sentences task assesses emotional biases in the individual’s tendency to interpret ambiguous information. We will employ the mouse-contingent version of the scrambled sentences task [135]. In this task, participants unscramble sentences using five of the six displayed words to form grammatically correct and meaningful statements (e.g., looks the future bright very dismal). By reporting the unscrambled sentence that first comes to mind, every sentence is resolved in either a positive (e.g., the future looks very bright) or negative (e.g., the future looks very dismal) manner. Twenty unscrambled sentences designed to tap into depression-relevant themes and 20 designed to tap into anxiety-related themes will be presented. An index of negative interpretation bias will be obtained from the ratio of negatively unscrambled sentences to the total correctly completed emotional sentences. The index of positive interpretation bias will be obtained from the ratio of positively unscrambled sentences to the total correctly unscrambled emotional sentences. Additionally, the mouse-contingent version of the task will also allow us to obtain indices of positive and negative attention bias through tracking of duration of time spent on negative versus positive words. Employing the mouse-contingent version of SST will allow us to assess attention biases for emotional stimuli in a reliable manner, and without additional burden for participants in the form an additional dot probe task to measure attention biases.

#### Pre-post ecological momentary assessment (EMA)

We will assess change from baseline to 10 weeks after the intervention in CAR using saliva samples obtained over a period of 2 days in a week at pre-test and post-test (please see Table 1). On two consecutive days (Thursday and Friday) of a given week, each day participants will provide saliva samples four times a day at the following timepoints: immediately after awakening, +30 minutes after awakening, +60 minutes after awakening, and once in the evening. Furthermore, on 8 days over a period of 2 weeks, 4 days (Thursday to Sunday) each in a week (including 2 days of the saliva samples), participants will receive 5 push notifications randomly jittered over the day on their mobile App to respond to EMA questions about stress assessment and stressor appraisal questions [209], coping or regulation strategy used if a stressor was present (using CERQ and Brief-COPE [210], affective state, valence and temporal orientation of thoughts, loneliness, perceived emotional control and interoceptive awareness. Additionally, for the cortisol samples, participants will be asked directly after the first sample after awakening about sleep quality, time of saliva assessment, hormonal cycle, current illness, work shift and work day/weekend in order to control for these variables. The pre-post EMA will take place at the participants’ location.

**Table 1 pone.0256323.t001:** An overview of all the different ecological momentary assessment (EMA) measures in the study, and the time and method of assessment.

Measured Variable	EMA Timepoint in the study	Assessment time	Assessment method	EMA Type
Diurnal Cortisol Profile	Pre- and Post-test	2 consecutive weekdays	immediately after awakening, +30 minutes after awakening, +60 minutes after awakening, in the evening	Event- and time sampling
Quality of sleep, stress assessment and stressor appraisal questions, CERQ, Brief-COPE, Affect Grid (affective state), emotional control, interoceptive awareness, Cube of Thoughts (valence, temporal and social orientation of thoughts), feelings of loneliness	Pre- and Post-test	Over 8 days in a period of 2 weeks, 4 days each in a week (Thursday-Sunday)	5 timepoints randomly jittered across the day	Time sampling
Time of Saliva Assessment, Hormonal Cycle, Current Illness, Jetlag, Shift Work and Work day/Weekend	Pre- and Post-test	On 2 days of cortisol sampling	After the first cortisol sample when awakening	Event Sampling
CERQ, Perceived Stress Scale– 4-item version (PSS-4), FoC Scale (only following subscales will be assessed: Fear of Expressing Compassion for Others and Fear of Expressing Kindness and Compassion Towards Oneself), S-SCS (only following subscales will be assessed: Self-Kindness and Common Humanity), Mindfulness scale (CAMS-R or FFMQ), MAIA (only following subscales will be assessed: Self-Regulation and Body Listening), IRI (only subscale Personal Distress will be assessed), Penn State Worry Questionnaire-3, Cognitive Control and Flexibility Questionnaire (CCFQ), Acceptance and Action Questionnaire (AAQ-II), Brief COPE, Inclusion of Other in the Self Scale (IOS Scale; (216), stress assessment and stressor appraisal questions (209), and three self-generated questions on frequency and quality of social interaction and empathic listening. (“How often did you have social contact last week?”, “How pleasant were these social contacts on average?”, “How well were you able to listen to the other person in this interaction?”)	Weekly assessment	Once a week, over the period of 10 weeks of intervention	Once a day	Time sampling
Affect Grid, Cube of Thoughts, feeling of connectedness to partner, level of interoception (awareness of bodily sensations), loneliness, feeling of engagement with the exercise (only post), and personal disclosure (only post Affect Dyad)	Pre and Post daily intervention exercise	Daily (feeling of engagement with the exercise), and every other day (all other variables) over the period of 10 weeks of intervention	Twice daily (6 times per week)	Event sampling

